Preoperatively, the physical status of all included participants will be assessed using the American Society of Anesthesiologists (ASA) scale. This classification identifies five classes of physical status depending on the presence of concomitant diseases (ranging from class I (healthy patient) to class V (dying).

In addition, the total cost of surgery and hospital stay will be calculated based on the cost of surgical intervention and inpatient treatment and the indirect cost of patients’ occupational disability. Two years postoperatively, the cost of subsequent treatment in the rehabilitation centre, additional treatment of possible postoperative complications, and/or treatment of other manifestations of degenerative spine disease as well as period of incapacity for work are to be considered.

All participants who have undergone spine instrumentation will be examined for intervertebral fusion parameters using the criteria of Tan et al. [13]; grade 1 corresponds to complete bone union, whereas grade 4 corresponds to pseudarthrosis. Moreover, the time of fusion development will be estimated.

Finally, sagittal balance parameters will be analysed in all patients, including pelvic tilt (PI), pelvic deviation from the vertical (PT), S1 vertebral tilt (SS), and vertical axis displacement (SVA).

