## Statistical methods

### Statistical methods for primary and secondary outcomes {20a}

The results will be analysed using the intention-to-treat principle. Statistical significance will be defined as *p* < 0.05 based on a two-sided test. No adjustments for multiple tests are planned. The normality of variables will be evaluated using the Shapiro-Wilk statistic. Student’s *t*-test (for normally distributed data) and Pearson’s chi-square test (for categorical data) will be used to reveal differences in symptom rates among the groups. Multiple linear regression will be used to measure point estimates and confidence intervals for group differences in the ODI and clinical scale scores from baseline to the 2-year follow-up.

The non-parametric Mann-Whitney *U* test will be used to reveal differences in continuous variables between groups both pre- and postoperatively. Continuous data within the groups will be compared using the Wilcoxon test. Categorical parameters among the groups will be compared using Fisher’s exact two-tailed test.

Complication incidence during the 2-year follow-up will be compared between groups using Kaplan–Meier survival curves and the log-rank test. The significance of the risk factors (predictors) for all registered complications will be evaluated using univariate and multivariate logistic regression models.

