### Methods for additional analyses (e.g., subgroup analyses) {20b}

No additional analyses are planned.

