## Discussion

Currently, the selection of surgical solutions for lumbar stenosis remains controversial. This study was designed to provide surgeons with high-level evidence by comparing the clinical outcomes of the two most popular treatment methods. The non-inferiority study design [14] was chosen because according to the current evidence [4, 5] and our experience, both methods are non-inferior (comparable) in terms of the primary endpoint, while there may be superiority in certain secondary endpoints, such as cost effectiveness and lower complication rates.

The non-inferior margin was chosen based on the minimum clinically important difference (MCID), which represents the smallest improvement considered worthwhile by a patient. For patients with lumbar spine stenosis, the MCID in ODI score ranges from 12.54 to 12.8 points [15, 16]. Therefore, a non-inferiority margin of *δ* = 12 was selected according to this data.

To develop the structure of this study, we did our best to maximise the homogeneity of the participant groups. For this purpose, we used precise inclusion and exclusion criteria and accurately restricted the range of surgical methods and postoperative rehabilitation treatment. The key role of postoperative rehabilitation in favourable clinical outcomes is widely known. In our study, all included participants are scheduled for rehabilitation treatment at the same rehabilitation centre within 3 months postoperatively. We believe that these conditions maximise the homogeneity of the participant groups and limit possible clinical outcomes by several factors. We suggest that the mentioned structure of the study implicates decompressive intervention as the only factor for favourable clinical outcomes compared to spinal fusion.

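### By its general wording the plan leaves the cost comparison to a Mann-Whitney test, which does not address the difference in mean cost

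*Protocol article*

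**What the plan says.** The methods are in the protocol article under Statistical methods for primary and secondary outcomes {20a}:

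- Mann-Whitney: the "test will be used to reveal differences in continuous variables between groups both pre- and postoperatively". The sentence lists no variables and makes no exception for cost.
- Normality: "The normality of variables will be evaluated using the Shapiro-Wilk statistic". The t-test (for normal data) and the chi-square test "will be used to reveal differences in symptom rates among the groups".
- Multiple linear regression, the only method there described as giving estimates with intervals, covers "confidence intervals for group differences in the ODI and clinical scale scores from baseline to the 2-year follow-up".

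Cost is described under Secondary endpoints. In hospital, "the total cost of surgery and hospital stay will be calculated based on the cost of surgical intervention and inpatient treatment", together with the indirect cost of lost work. Over two years the protocol adds rehabilitation, "additional treatment of possible postoperative complications, and/or treatment of other manifestations of degenerative spine disease", and time off work.

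The Discussion justifies the non-inferiority design partly because "there may be superiority in certain secondary endpoints, such as cost effectiveness and lower complication rates". Background and rationale {6a} also lists the economic efficiency of decompression among the reasons for the trial.

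**The concern.** Whether decompression saves money is a question about mean cost: total spending divided by patients treated. Mann-Whitney asks instead whether a randomly chosen decompression patient tends to cost less than a randomly chosen fusion patient.

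The two questions can have different answers when most patients in one arm are slightly cheaper and a few are much dearer. A re-operated patient takes one of the top ranks whether the re-operation costs twice or ten times the index procedure. The protocol deliberately collects two years of complication and re-treatment costs, and a rank test largely ignores how large they are.

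This matters because a non-inferiority result persuades through offsetting advantages, and cost is one that this protocol names. A significant rank test could be reported as lower cost without showing it.

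**Working it through.** **Does another stated method reach cost?** Regression is limited to the ODI and clinical scales. The t-test sentence concerns symptom rates in normal data. If the Shapiro-Wilk check is read as a gate for every variable, right-skewed cost would tend to fail it and go to Mann-Whitney anyway. No named method targets mean cost.

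**Inputs from the protocol.** Sample size {14} gives 43 per arm as planned and 70 in total (35 per arm) before the allowance for 20% missing follow-up. Tests are two-sided at 0.05. The protocol gives no cost figures, so it has none to reproduce.

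**Assumed inputs.** Index cost is lognormal with mean 1.0 (decompression) and 1.3 (fusion) and the same coefficient of variation (CV) in both arms. A re-operation adds 3.0.

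- Scenario A, 10% versus 0% re-operated: means 1.0 + 0.10 × 3.0 = 1.30 versus 1.30, equal.
- Scenario B, 15% versus 0%: 1.0 + 0.15 × 3.0 = 1.45 versus 1.30. Decompression is 0.15 dearer, and 0.15/1.30 is about 11%.

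**What the rank test estimates.** Let θ be the probability that a decompression patient costs less than a fusion patient. With log-scale SD σ = √ln(1 + CV²), and treating any re-operated patient as dearer than every fusion patient,

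θ ≈ (1 − p) × Φ( ln 1.3 / (σ√2) ), where p is the re-operated share.

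At CV 0.2, σ = √ln 1.04 = 0.198, so Φ(0.262/0.280) = 0.826. In scenario A, θ ≈ 0.90 × 0.826 = 0.74. At CV 0.5, σ = 0.472, Φ(0.262/0.668) = 0.653 and θ ≈ 0.59.

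With n = 43 per arm, the null standard error of the estimate of θ is √[(2n + 1)/(12n²)] = √(87/22,188) = 0.063. The test is therefore significant above about 0.5 + 1.96 × 0.063 = 0.62. The first case lies well above that threshold and the second a little below it.

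The re-operation cost of 3.0 does not enter θ. If it were 6.0, decompression's mean in scenario A would be 1.0 + 0.10 × 6.0 = 1.60, about 23% dearer than 1.30, with essentially the same rank-test result.

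**Simulation.** 20,000 trials per cell (Monte Carlo standard error at most 0.4 percentage points). Share of trials with p < 0.05 in favour of decompression:

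| Scenario | Test | Per arm | CV 0.2 | CV 0.3 | CV 0.5 | CV 0.8 |
|---|---|---|---|---|---|---|
| A, equal means | Mann-Whitney | 43 | 98% | 75% | 29% | 11% |
| A, equal means | Mann-Whitney | 35 | 95% | 66% | 25% | 10% |
| A, equal means | Welch | 43 | 7% | 6% | 4% | 3% |
| A, equal means | Welch | 35 | 8% | 7% | 4% | 3% |
| B, decompression 11% dearer | Mann-Whitney | 43 | 91% | 53% | 15% | 5% |
| B, decompression 11% dearer | Mann-Whitney | 35 | 84% | 45% | 13% | 5% |
| B, decompression 11% dearer | Welch | 43 | 1% | 1% | 1% | 1% |
| B, decompression 11% dearer | Welch | 35 | 2% | 1% | 1% | 1% |

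With equal means, a correct test of means would favour decompression in 2.5% of trials.

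**Without zero re-operations after fusion.** With 15% versus 5% re-operated (equal means of 1.45), Mann-Whitney at 43 per arm favours decompression in 94%, 63%, 23% and 9% of trials across the same CVs.

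**The case against.** - **Cost is not named in the test sentence.** This stands. Cost is covered only by general wording, and other continuous outcomes (the ODI and clinical scales) also get regression. A reader might infer that the plan makes Mann-Whitney the sole test for all continuous variables and expressly assigns cost to it. The text supports neither.
- **The economic method may sit in a fuller document.** This stands in part. A rank test cannot deliver the cost-effectiveness result the Discussion mentions, so more may be planned elsewhere. The statement "No additional analyses are planned" falls under a heading about subgroup-type analyses and does not clearly exclude it. But the point is about the scope of a test the protocol does state, not about missing detail.
- **The large percentages depend on one assumption.** This stands. A reader might take 98% or 91% as the likely error rate. Nothing in the documents supports a CV of 0.2, and a cost built from stay, rehabilitation, complications and lost work could well spread more widely. At CV 0.8 the figures are 11% and 5%.
- **The scenario runs against the protocol's own evidence.** This stands. Background and rationale {6a} cites lower two-year payments and fewer complications with decompression. The reversal needs more costly late events after decompression, which is possible but not documented here. A reader might infer that the trial will wrongly call decompression cheaper; the documents do not support that.
- **Costly events would remain visible.** This stands in part. Complications are compared by Kaplan–Meier and log-rank, Table 2 records repeat surgeries and cost components, and nothing forbids reporting mean costs. None of this makes the rank-test p-value a test of mean cost.

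**Conclusion.** The concern holds in a limited form. As worded, the plan would compare in-hospital and two-year cost by a test of rank order, while the economic argument it is meant to support needs the difference in means. The mismatch does not depend on any assumed figure.

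How often it would mislead does. In the assumed pattern (cheaper index operation, more late re-operations), the chance of a significant result for decompression at 43 per arm runs from 98% down to 11% when mean costs are equal, and from 91% down to 5% when decompression is about 11% dearer, as CV rises from 0.2 to 0.8. At 35 per arm the figures are mostly somewhat lower. If the arms differ as the cited evidence suggests, both tests would tend to point the same way.

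Severity is minor to moderate: cost is a secondary outcome, and the primary conclusion rests on the ODI.

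**What to change.** State in the statistical methods section that, for in-hospital cost and for two-year total cost, the main comparison is the difference in arithmetic mean cost between arms with a non-parametric bootstrap 95% confidence interval, and that any Mann-Whitney result on cost is descriptive only.

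This takes a sentence and a few lines of code, with no new data and no change in sample size. The downside is a wider, less favourable interval than the rank-test p-value suggests. In scenario B at 43 per arm, a Welch test finds decompression significantly dearer in only about 8% of trials, so an inconclusive cost result is a realistic outcome. With only a handful of very expensive patients, interval coverage will also be approximate: the Welch rates of up to 7–8% under equal means, against 2.5%, show the same small-sample limit.

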### Secondary endpoints

The SF-36 v.1 scale (standard form) provides a comprehensive evaluation of the quality of life both pre- and postoperatively [8]. The SF-36 questionnaire consists of 36 questions grouped into eight sections assessing physical functioning, role functioning, bodily pain, general health condition, vitality, social functioning, emotional state, and mental health. The maximum score of each section is limited to 100 points. These eight scales will be aggregated into two summary measures: physical (PH) and mental (MH) health summary scores.

Another scale assessing participants’ quality of life is the EQ-5D-5L [9]. This questionnaire is widely used in multiple prospective European studies focusing on lumbar stenosis treatment. Currently, we believe this scale is applicable for comparing our results with literature data. The EQ-5D-5L questionnaire consists of five sections (mobility, self-care, usual activities, pain, and anxiety) comprising five levels per section, supplemented with the EQ-VAS visual analogue scale. The obtained results can be easily converted into a single numerical value (index) adjusted for the patient’s region of residence. Currently, there are no approved values for calculating this index in the Russian Federation (https://euroqol.org). Therefore, at baseline, a simple comparison of the specific numerical values for each parameter will be applied. If feasible, we will calculate this index at the end of the study.

The Won-Korff Chronic Pain Syndrome Assessment Scale (Chronic Pain Grade Questionnaire, CPGQ) [10] is focused on the assessment of pain severity and its impact on participants’ quality of life. Grade 0 corresponds to the absence of pain, while grade IV corresponds to a severe decrease in the quality of life due to severe pain.

The Pain Catastrophizing Scale (PCS) [11] was created to estimate the psychological aspects of pain perception, attenuating the exaggerated negative perception of painful stimuli. The questionnaire contains 13 questions assessed in points (ranging from 0 points (no symptoms) to 4 points (negative perception is experienced constantly).

The Chronic Pain Coping Inventory (CPCI) [12] includes 64 questions, allowing one of eight alternative scales to differentiate between participants’ preferred strategies for managing chronic pain.

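### The analysis section has no rule for ordered grades, so the CPGQ (grades 0 to IV) most naturally falls to Fisher's exact test, which ignores the order and costs power

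*Protocol article*

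**What the plan says.** Under Secondary endpoints, the protocol describes the CPGQ result only as a grade: "Grade 0 corresponds to the absence of pain, while grade IV corresponds to a severe decrease in the quality of life due to severe pain". It describes no numerical CPGQ score.

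The section Statistical methods for primary and secondary outcomes {20a} then assigns tests by type of variable:

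- Normally distributed data go to Student's t-test.
- For the Mann-Whitney U test, the wording is "test will be used to reveal differences in continuous variables between groups both pre- and postoperatively".
- For categorical data there are two sentences. One is "Pearson’s chi-square test (for categorical data) will be used to reveal differences in symptom rates among the groups". The other is "Categorical parameters among the groups will be compared using Fisher’s exact two-tailed test".
- Multiple linear regression is to supply point estimates and "confidence intervals for group differences in the ODI and clinical scale scores from baseline to the 2-year follow-up".

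Table 2 lists ODI, SF-36, EQ-5D-5L and ASA as clinical measures, and CPGQ, PCS and CPCI as psychological measures.

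**The concern.** A five-grade outcome is neither continuous nor normally distributed. Read literally, {20a} therefore treats the CPGQ grade as a categorical parameter and sends it to Fisher's exact test. That test, like Pearson's chi-square, asks whether the two grade distributions differ in any way at all. It spreads its sensitivity over up to four degrees of freedom and returns no direction and no effect estimate.

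The difference of interest here is a shift towards better or worse pain grades in one group. With 35 to 43 patients per group, an order-blind test will miss such a shift more often than a test that uses the order. A real difference in pain grade between the operations could then be reported as no difference.

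**Working it through.** **Step 1. Which test does the text imply for the CPGQ?**

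- The rank test is reserved for continuous variables, and a grade from 0 to IV is not one.
- Fisher's exact test is given for categorical parameters without qualification.
- Chi-square is tied to symptom rates, so it fits a graded scale less well than Fisher.
- The regression sentence covers the ODI and clinical scale scores. Table 2 puts the CPGQ outside the clinical measures, but nothing says that {20a} uses the word clinical in the sense of that table.

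Fisher's exact test is the most natural reading, but not the only one.

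**Step 2. Is there a figure in the plan to reproduce?** No. The protocol states no power, effect size or grade distribution for the CPGQ. The only inputs it supplies are the two-sided 5% level ({20a}) and the group sizes (Sample size {14}): 86 / 2 = 43 enrolled and 70 / 2 = 35 evaluable per group. Everything else below is assumed.

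**Step 3. Assumed model.** There are five ordered grades. One group has cumulative probabilities C_j; in the other, the cumulative odds C_j / (1 − C_j) are multiplied by a common odds ratio (OR). For example, with 20% in each grade and OR 3:

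- cumulative odds 0.25, 0.667, 1.5, 4 become 0.75, 2, 4.5, 12;
- cumulative probabilities become 0.429, 0.667, 0.818, 0.923;
- the grades then hold about 42.9%, 23.8%, 15.2%, 10.5% and 7.7%.

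Five reference distributions (grades 0 to IV, %) were used: 20/20/20/20/20, 10/20/40/20/10, 15/35/25/15/10, 5/15/25/30/25 and 30/35/20/10/5.

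**Step 4. Tests compared.** Here n and m are the group sizes, N = n + m, and t_j is the total in grade j.

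- Tie-corrected Mann-Whitney: W is the sum of midranks in one group, with mean n(N + 1)/2 and variance (nm/12)[(N + 1) − Σ(t_j³ − t_j)/(N(N − 1))]. Reject if the standardised value exceeds 1.96 in absolute size.
- Pearson chi-square: Σ(O − E)²/E, with degrees of freedom equal to the number of occupied grades minus 1.
- Fisher's exact test for a 2 × 5 table (Freeman-Halton): the probability, given the margins, of all tables no more likely than the one observed, estimated by Monte Carlo.

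Permuting the grades leaves the last two p-values unchanged; only the first uses the order. Each scenario had 20,000 replicates for the first two tests and 1,500 for Fisher. The simulation standard error at 50% power is √(0.25/20,000) ≈ 0.4 points and √(0.25/1,500) ≈ 1.3 points.

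**Step 5. Results, even distribution (power, %).**

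| n per group | OR | Mann-Whitney | Chi-square | Fisher | Loss, Fisher (points) |
|---|---|---|---|---|---|
| 35 | 2.0 | 36.5 | 21.1 | 21.5 | 15.0 |
| 35 | 2.5 | 56.2 | 34.4 | 34.1 | 22.1 |
| 35 | 3.0 | 71.8 | 48.2 | 46.5 | 25.3 |
| 35 | 3.5 | 80.9 | 59.6 | 59.9 | 21.0 |
| 35 | 4.0 | 88.5 | 70.1 | 70.8 | 17.7 |
| 43 | 2.0 | 44.2 | 25.6 | 26.1 | 18.1 |
| 43 | 2.5 | 65.4 | 42.6 | 41.2 | 24.2 |
| 43 | 3.0 | 80.4 | 59.4 | 58.1 | 22.3 |
| 43 | 3.5 | 88.9 | 71.3 | 70.7 | 18.2 |
| 43 | 4.0 | 94.1 | 80.6 | 80.2 | 13.9 |

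**Step 6. All five distributions.** Over OR 2 to 4, the loss of either unordered test runs from 11.3 points (30/35/20/10/5, n = 43, OR 4, Fisher) to 25.3 points (even, n = 35, OR 3, Fisher). Where the rank test has 53% to 82% power (OR 2.5 to 3.5 at n = 35; OR 2.5 to 3 at n = 43), the loss is 18.7 to 25.3 points and mostly above 20. Elsewhere it is mostly 11 to 20.

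**Step 7. No effect (OR 1).** Rejection rates were 4.7–5.2% (Mann-Whitney), 4.1–4.9% (chi-square) and 4.2–5.7% (Fisher). The unordered tests buy no better error control.

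**The case against.** The strongest reply is that the protocol never says the CPGQ will be tested with Fisher's exact test. It calls the instrument a scale, plans regression for scale scores, and is a condensed article whose analysis plan may settle which test goes with which instrument. This stands in part: the assignment is an inference and should be presented as one. It does not remove the point, because {20a} does state a rule for categorical parameters, makes no exception for ordered ones, and keeps the rank test for continuous variables. If regression was meant for the CPGQ, the text still supports two different analyses of one endpoint.

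Four stronger readings are tempting, and the documents do not support them:

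- **That the EQ-5D-5L items have the same problem.** They have five levels each, but the protocol says that at baseline "a simple comparison of the specific numerical values for each parameter will be applied", with an index at the end if feasible, and Table 2 lists the instrument as clinical. Numerical handling is the more natural reading, so the point reaches these items only if they are analysed by level.
- **That the loss is 20 to 25 points throughout.** That holds mainly for mid-range effects. The grade distributions and effect sizes are assumed, and the proportional-odds shift itself favours the rank test.
- **That the trial is counting on superiority in pain grade.** The Discussion's examples of possible secondary superiority are cost effectiveness and complication rates.
- **That the non-inferiority conclusion is at risk.** The primary endpoint is the ODI, which this does not touch. Pain is also captured by SF-36 bodily pain and the EQ-5D-5L pain item.

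It is also fair to say that a bare Mann-Whitney p-value gives no effect estimate either. That is a reason to prefer the ordinal model.

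**Conclusion.** The point holds for CPGQ grades, as a minor improvement to one secondary endpoint. {20a} has no rule for ordered grades, and the one it states leads most naturally to a test that ignores their order. The power loss in Step 6 rests on the proportional-odds shift and on grade distributions and odds ratios that the protocol does not give. The direction of the loss for a consistent shift in grade is secure; its exact size in this trial is not known. Severity is low.

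**What to change.** In {20a}:

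- Limit Fisher's exact and Pearson's chi-square tests to binary or unordered variables.
- State that CPGQ grades are compared between groups with a proportional-odds model that includes the baseline grade, reporting the common odds ratio with its 95% confidence interval. The simple alternative is the tie-corrected Mann-Whitney test, which is already in the plan but would have to be extended beyond continuous variables.
- Apply the same rule to EQ-5D-5L items only if they are analysed by level.

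The cost is a few sentences, with no new data, visits or patients. There are two drawbacks: an ordinal analysis is less sensitive to a difference that is not a consistent shift (for example, more patients at both extremes in one group), and the proportional-odds assumption has to be checked.
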